### Subject withdrawal

The subjects may choose to withdraw from the study, or they may be withdrawn from the study, at any time at the discretion of the investigator. If a subject withdraws or is withdrawn, every effort will be made to complete and report the observations as thoroughly as possible.

The possible reasons for withdrawal include (but are not limited to) (1) subject’s decision, (2) intolerable adverse events, (3) clinically significant laboratory abnormality, (4) protocol violation (e.g., incorrectly enrolled or randomized), (5) subject requires use of unacceptable concomitant medication, (6) subject not compliant with protocol procedures, (7) subject develops a condition during the study that violates the inclusion and exclusion criteria (e.g., pregnancy), (8) death and/or (9) any other reason, in the investigator’s opinion, that would impede the subject’s participation in the study.

In the event of pregnancy, the subject will be monitored until the conclusion of the pregnancy, and the outcome of the pregnancy will be reported. If a subject ends her participation in the study before randomization (before the first treatment visit), she will be replaced by another randomly selected patient. If this happens, the situation and circumstances will be documented in the case report form.

### Statistical methods

#### Sample size calculation

Two types of sample size calculations were performed: non-repeated measures and repeated measures. Our primary outcome of interest is the difference in proportion of responders between the active and sham groups after 8 weeks of treatment, defined as a reduction of 5 points or more from baseline to 8 weeks in the ICIQ-UI-SF total score. On the basis of outcomes derived from previously published data on MS, it is anticipated that MS will improve symptoms in 60 % (p1 = 0.6) of subjects with SUI, whereas sham MS will improve symptoms in 30 % (p2 = 0.3) of subjects with SUI [11, 13]. Thus, a minimum sample size of 88 (44 per arm) is powered to detect a difference of at least 30 % (δ = 0.3), with a 95 % confidence interval (α = 0.05) and statistical power of 80 % (β = 0.2) [38]. Allowing for a 25 % dropout rate, the enrollment goal is 120 subjects.

We also calculated our sample size using PASS^13^ Sample Size Software (NCSS Statistical Software, Kaysville, UT, USA) [39]. The tests for two proportions in a repeated-measures design, which can be used to calculate sample size in a mixed-model analysis of repeated measures data, was selected from among the PASS^13^ statistical tools. Using the same parameters (δ = 0.3, α = 0.05 and β = 0.2), an autoregressive AR(1) covariance pattern with autocorrelation of 1.0, and a design with six repeated measurements, a total sample size of 84 (*n* = 42 in each arm) was obtained. As the sample size calculated using a test of simple differences in proportion was higher, we selected the initial calculated sample size.

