The main outcome measure (responder analysis of ICIQ-UI-SF, dichotomous variable) and other dichotomous variables will be analyzed using GLMM (binomial logistic regression). We will estimate the marginal means of proportions, odds ratios comparing treatments and the corresponding 95 % confidence intervals. The fixed effects include time, code and interactions between code and time. Code comprises two binary coded variables, with the sham group set as the reference group. We are primarily interested in the code and time interaction, which represents the difference in outcome variables between groups.

For responder analysis of outcome measures, subjects who withdraw after randomization (missing data) will be considered as treatment failures and will be included in the denominator. The responder analysis between treatment groups will be compared using GLMM (binary logistic regression).

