## Discussion

Our trial is a prospective, randomized, double-blind, sham-controlled trial of SUI using pulsed MS. The trial is adequately powered and will use validated outcomes. Previous studies conducted with MS had inherent flaws, resulting in inconclusive evidence on this treatment modality. A search of trial registers indicates that there are currently no ongoing, prospective clinical trials investigating our research question of interest (last search done on 5 December 2014).

There is a need for a high-quality randomized clinical trial on this topic with a sham group, adequate sample size, appropriate methodology and validated outcome measures, as well as long-term follow-up [19]. We intend to address the shortcomings of previous studies in our trial and to obtain convincing evidence on the efficacy of MS. We acknowledge the importance of applying a sham MS as a control. We will use a specially designed MS device for the purposes of this trial. The appearance and noise are identical to the active treatment. The sum of energy output of the 8-week sham treatment is lower than the sum of energy output of one 20-minute active mode run ([name], personal communication). Furthermore, we will recruit only subjects who are naive to MS. All subjects will be told that they may experience a tingling sensation. Subjects will also be assessed for effectiveness of blinding at the end of the 8-week treatments. To further allow for double-blinding, all assessors involved in the study will be deliberately prohibited from entering the treatment room, and treatment will be coordinated by independent study nurses. Collectively, these measures allow better blinding of subjects with the aim to diminish the placebo effects.

Next, we determined our sample size based on a priori calculation to ensure that our study is adequately powered to answer our primary outcome of interest. To evaluate the effects of MS on SUI, we selected various subjective and objective outcome measures as recommended by international guidelines [44, 45]. Further, we chose a patient-reported outcome, the ICIQ-UI-SF questionnaire, as our primary outcome measure because we recognize the importance of judging treatment benefit from a patient’s perspective [24]. We hope that use of standardized, internationally accepted tools will ease data pooling in meta-analyses, limiting the number of high-quality clinical trials required to draw concrete conclusion on this treatment option.

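### The enrolment goal of 120 is inflated as if dropouts leave the analysis, but the primary responder analysis counts them as failures; power is about 75% if 25% are missing by week 8

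*Protocol article*

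**What the plan says.** In the protocol article, Sample size calculation, the quantity being powered is given as: "Our primary outcome of interest is the difference in proportion of responders between the active and sham groups after 8 weeks of treatment". The assumed rates are "MS will improve symptoms in 60 % (p1 = 0.6) of subjects with SUI" and "sham MS will improve symptoms in 30 % (p2 = 0.3) of subjects with SUI". From these, with α = 0.05 and 80% power, the section obtains 88 women (44 per arm). It then allows for a 25% "dropout rate, the enrollment goal is 120 subjects".

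In Statistical analysis, all randomised women are compared by intention to treat. For responder outcomes the rule is that "subjects who withdraw after randomization (missing data) will be considered as treatment failures and will be included in the denominator". The same section calls the main outcome a responder analysis of the ICIQ-UI-SF, so this rule covers the primary comparison. An earlier paragraph of that section says that missing data will not be imputed.

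The Discussion relies on the calculation: "The trial is adequately powered and will use validated outcomes".

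**The concern.** The sample size section and the analysis section treat a dropout in two different ways. Dividing the required number by one minus the dropout rate is the right correction when a dropout costs an observation and nothing else: the sample shrinks and the treatment difference stays the same. Under the failure rule the sample does not shrink. All 120 women are analysed, and each withdrawal adds a non-responder. Both response rates are pulled towards zero, and the difference between them shrinks in proportion to dropout. Nothing in the sample size section lowers the rates or the 30-point difference to allow for this.

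At stake is the stated 80% power for the primary comparison, and so how a non-significant primary result would be read in a trial described as adequately powered.

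**Working it through.** **Inputs.** From Sample size calculation: 60% versus 30%, α = 0.05, power 80%, 44 per arm, 25% dropout, 120 enrolled. From Randomization: 1:1 allocation, so 60 per arm. From Statistical analysis: withdrawals count as failures. The test is taken as two-sided, which is not stated; a one-sided test would need 33 per arm and does not fit the stated 44.

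**Formula.** Power of the two-proportion test with pooled variance under the null:

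power = Φ{ [ (p1 − p2)√n − 1.960·√(2·p̄·(1 − p̄)) ] / √( p1(1 − p1) + p2(1 − p2) ) }, where p̄ = (p1 + p2)/2 and n is the number per arm.

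This stands in for the week-8 contrast from the planned mixed logistic model.

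**Step 1: reproduce the plan's figure.**
- The pooled formula at 0.60 versus 0.30 needs 41.97, so 42 per arm. The variant that uses p̄ for both variance terms gives (1.960 + 0.842)² × 2 × 0.45 × 0.55 / 0.30² = 43.17, which rounded up to 44 is the stated number.
- At 44 per arm the power is 81.9%. The stated size is sound for its own assumptions.
- Inflation: 88 / 0.75 = 117.3, taken up to 120. In reverse, 120 × 0.75 = 90, or 45 per arm, and power at 60% versus 30% is 82.8% (81.8% by exact enumeration of the chi-square test). If dropouts are excluded, the 80% claim holds.

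**Step 2: apply the failure rule.** Assume 25% missing in each arm at week 8, and 60% and 30% among those with data.
- Active: 0.60 × 0.75 = 0.45. Sham: 0.30 × 0.75 = 0.225. Difference: 0.225.
- p̄ = 0.3375; (p1 − p2)√60 = 1.743; 1.960 × √(2 × 0.3375 × 0.6625) = 1.311; √(0.2475 + 0.1744) = 0.6495.
- Power = Φ[(1.743 − 1.311) / 0.6495] = Φ(0.665) = 74.7%.
- Other tests: 75.3% (chi-square, exact enumeration) and 74.4% (Wald test of the log odds ratio, the closest of these to logistic regression).
- For scale only, 80% power under these assumptions corresponds to 68.1, so 69 per arm.

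**Step 3: vary the dropout by week 8** (equal in both arms, 60 per arm).

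| Missing at week 8 | Rates compared | Power |
|---|---|---|
| 10% | 54% v 27% | 86.3% |
| 15% | 51% v 25.5% | 82.8% |
| about 18.5% | 48.9% v 24.5% | 80% |
| 20% | 48% v 24% | 78.9% |
| 25% | 45% v 22.5% | 74.7% |

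**Step 4: unequal dropout.** With 30% missing on active and 20% on sham, power is 55.5%. With the split reversed, it is 88.5%. The article gives no expected split.

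**Step 5: the other reading of the rates.** If 60% and 30% are rates among all randomised women, with withdrawals already counted as failures, then 60 per arm at 60% versus 30% gives 92.1%, and inflation for dropout was not needed.

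**The case against.** The strongest reply is that the shortfall depends on inputs the article does not give.

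- **Timing.** The 25% is not tied to week 8. Table 1 runs follow-up to week 32, and the Discussion intends at least one year. The primary comparison is at week 8. Subject withdrawal and Quality control and monitoring both describe efforts to keep collecting data from women who stop. Dropout by week 8 could well be under 18.5%, and power would then be at least 80%. This stands, and it is why the 75% must be conditional.
- **Meaning of the rates.** The text speaks of subjects with SUI, without saying whether they are completers or all randomised. The completer reading is inferred from the inflation step. This also stands; the other reading gives about 92% and makes the inflation merely conservative.
- **The no-imputation statement.** If it governed the primary analysis, dropouts would contribute no week-8 value and the inflation would be roughly right (82.8% at 45 per arm). But the failure rule is the specific one for responder outcomes, so it is followed here. The two statements do need reconciling.
- **Proxy.** The figures come from a two-proportion test, not the planned repeated-measures model. For a week-8 contrast this is a reasonable stand-in, but no more than that.

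A reader might also infer that the repeated-measures calculation, with "an autoregressive AR(1) covariance pattern with autocorrelation of 1.0, and a design with six repeated measurements", is a failed independent check. It does largely return the single-visit answer, but the article does not call it a check and sets it aside for the larger number, so nothing in the design depends on it.

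**Conclusion.** The mismatch is real: the enlargement from 88 to 120 rests on one treatment of dropouts and the primary responder analysis uses another. The plan's own arithmetic is not at fault; 44 per arm and 120 both reproduce.

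The size of the problem is conditional. Power is about 75%, some 5 points below the stated 80%, if 60% and 30% are rates among women with outcome data and 25% are missing in each arm by week 8. It is at or above 80% if no more than about 18.5% are missing by then, and about 92% if the two rates already count withdrawals as failures.

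A reader might infer that the trial is simply underpowered at 75%. The article does not support that, because it fixes neither the timing and split of dropout nor the meaning of the rates. What it does support is that the sample size statement does not describe the power of the analysis it precedes. The point is worth correcting, but it is modest.

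**What to change.** In Sample size calculation:

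1. State whether 60% and 30% are responder rates among women with week-8 data or among all randomised women with withdrawals counted as failures.
2. State the dropout expected by week 8, separately from dropout over the whole follow-up.
3. Restate the power of 120 women under the failure rule. If the rates are among women with data, that is about 75% at 25% dropout, 79% at 20% and 83% at 15%, assuming equal dropout in the two arms. If they are all-randomised rates, it is about 92%, and the text should say that the inflation was a margin and not a requirement.
4. Bring the claim of adequate power in the Discussion into line.

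The change is to wording only. Recruitment is complete and no more women are needed. The cost is that the stated power may be slightly less favourable. The primary missing-data rule should not be switched to an observed-data analysis in order to keep the 80% figure: that would change the primary analysis after recruitment has ended, and it would need its own justification.

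### With an autocorrelation of 1.0, the repeated-measures sample size of 84 is the ordinary two-proportion figure, so 80 % power is shown for the week-8 difference and not for the interaction named as the effect of interest

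*Protocol article*

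**What the plan says.** All references are to the Protocol article, Statistical methods.

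- **Quantity sized** (Sample size calculation): "the difference in proportion of responders between the active and sham groups after 8 weeks of treatment". The assumptions are that "MS will improve symptoms in 60 % (p1 = 0.6) of subjects with SUI" and "sham MS will improve symptoms in 30 % (p2 = 0.3) of subjects with SUI", with alpha 0.05 and 80 % power. This gives 88 (44 per arm), raised to 120 for 25 % dropout.
- **Second calculation** (same section): a software procedure for two proportions in a repeated-measures design, described as usable for mixed-model analyses. It keeps the same difference, alpha and power and adds "an autoregressive AR(1) covariance pattern with autocorrelation of 1.0, and a design with six repeated measurements". The outcome: "a total sample size of 84 (*n* = 42 in each arm) was obtained".
- **Choice between them** (same section): "As the sample size calculated using a test of simple differences in proportion was higher, we selected the initial calculated sample size".
- **Analysis** (Statistical analysis): the responder endpoint goes into a binomial GLMM with fixed effects for time, code (treatment) and their interaction, and "We are primarily interested in the code and time interaction".

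**The concern.** An autocorrelation of 1.0 means that each woman has the same response status at every visit. The covariance matrix is then singular and repeated measurement adds nothing. The Statistical analysis section itself warns that a constant correlation over time may be unrealistic, and AR(1) at 1.0 is the extreme case of that. Yet the article presents the result as a second type of calculation and takes the larger of the two, so a reader will believe that power was checked for the longitudinal model.

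What is at stake is the primary test more than the number of women. If the 80 % was shown only for a single-visit comparison while the model's headline term is an interaction, the trial could be judged on a test whose power was never assessed and whose null hypothesis differs from the one that was sized.

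**Working it through.** **Inputs.** From Sample size calculation: p1 = 0.60, p2 = 0.30, alpha = 0.05 (sidedness not stated; two-sided reproduces the figures), power 0.80, AR(1) with rho = 1.0, M = 6 measurements. The mean proportion is 0.45. Assumption: the procedure sizes a time-averaged difference.

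**1. Reproducing 84.** Pooled two-proportion formula for one visit:

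n = [1.96 × √(2 × 0.45 × 0.55) + 0.8416 × √(0.24 + 0.21)]² / 0.30² = 41.97, so 42 per arm and 84 in total.

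For a time-averaged difference this is multiplied by f = Σ rho^|i−j| / M², summed over all pairs of visits. At rho = 1 every term is 1, so f = M²/M² = 1 for any M. The repeated-measures answer is again 42 per arm, as stated.

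**2. Reproducing 88.** The same comparison with the pooled variance in both terms:

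n = 2 × 0.45 × 0.55 × (1.96 + 0.8416)² / 0.30² = 43.17, so 44 per arm and 88 in total.

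The gap between 84 and 88 is thus a difference between variance formulas for one test. By the pooled formula, power is 80.0 % at 42 per arm and 81.9 % at 44.

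**3. Dependence on the autocorrelation.** The article gives no other value, so the range below is assumed. Total N for a time-averaged difference:

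| rho | 6 measurements | 5 measurements |
|---|---|---|
| 0.5 | 34 | 38 |
| 0.7 | 48 | 52 |
| 0.8 | 58 | 62 |
| 0.9 | 70 | 72 |
| 0.95 | 78 | 78 |
| 1.0 | 84 | 84 |

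Every value below 1 gives a smaller N, so 84 is a ceiling for that target. The five-measurement column is relevant because Table 1 has six ICIQ-UI-SF times only if week 0 is counted. A change-from-baseline responder exists at weeks 4, 8, 12, 20 and 32. At rho = 1 the count makes no difference.

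**4. Enrolment.** 88 / (1 − 0.25) = 117.3, so 118, which supports 120.

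**5. What the interaction tests.** With responder status defined only at the five post-baseline visits, the code-by-time interaction asks whether the arm difference changes between visits. If the rates were already 60 % v 30 % at week 4 and stayed there, the week-8 difference would be 30 points and the interaction exactly null. Nor can rho = 1 size such a term: the variance of a within-woman change between adjacent visits is proportional to 2(1 − rho), which is 0.

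**6. Illustration only.** Assume week-4 rates of 45 % v 25 %, week-8 rates of 60 % v 30 %, 60 per arm and a between-visit correlation of 0.5 or 0.7. None of the week-4 rates or correlations is in the article. On the difference scale, the contrast is (0.60 − 0.45) − (0.30 − 0.25) = 0.10. The variance of change in each arm is p₄q₄ + p₈q₈ − 2·rho·√(p₄q₄p₈q₈), where q = 1 − p.

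- rho = 0.5: 0.2438 (active) + 0.1991 (sham); SE = √(0.4429/60) = 0.0859; power about 21 %.
- rho = 0.7: 0.1463 + 0.1197; SE = √(0.2660/60) = 0.0666; power about 32 %.
- If the 30-point gap is already present at week 4, the contrast is 0 and the rejection rate is the 5 % significance level.

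**The case against.** The strongest reply is that nothing in the trial's size depends on this input. The 84 was set aside and the 88 and 120 both reproduce. For a time-averaged difference, 1.0 is the least favourable autocorrelation, so the calculation errs on the large side. All of that stands. A reader might infer that 84 is a wrong number or that the trial is too small. The article supports neither: 42 per arm is a valid size for 60 % v 30 % at one visit, which is the stated primary comparison.

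A reader might also infer that the 84 was intended to size the interaction. The text does not say so. It carries over the same 0.3 difference in responder proportions. The interaction appears only in the analysis section, and the mismatch would remain if the 84 were deleted.

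Third, the article describes the interaction as representing the between-group difference in outcome, and the reference time is not given. With baseline as reference, the week-8 interaction term would be the arm difference in change from baseline. That holds for a continuous score. It does not rescue the responder endpoint, which is itself a change from baseline and has no informative baseline value.

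Finally, the interaction powers in step 6 rest on assumed rates and correlations. They show that the 80 % does not transfer; they do not estimate this trial's power. It is also fair that the exact match at 42 does not identify the software's formula: an arcsine calculation gives 41.79, which also rounds up to 42.

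**Conclusion.** The point holds in a limited form. The repeated-measures calculation is degenerate. On the assumption that it targets a time-averaged difference, it returns the plain two-proportion size, so comparing 84 with 88 does not compare two designs and does not verify power for the planned GLMM. This is an uninformative input rather than faulty arithmetic, and its effect on enrolment is nil.

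The part that matters for the trial's conclusion is the mismatch between sections. The stated 80 % belongs to the week-8 difference in responder proportions. The effect named as of primary interest is an interaction that, for this endpoint, can be null when the week-8 difference is the full 30 points. That follows from the definition of the endpoint and the visit schedule and needs no assumed rates.

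**What to change.** 1. In Sample size calculation, delete the repeated-measures calculation and the sentence comparing it with 88. If a mixed-model calculation is kept, redo it for the week-8 contrast with five post-baseline visits and a stated range of correlations below 1.
2. State there that 80 % power refers to the week-8 difference in responder proportions.
3. In Statistical analysis, name the week-8 active-v-sham contrast estimated from the GLMM as the primary test, in place of the code-by-time interaction.
4. If power for an interaction is mentioned anywhere, label it as an illustration under assumed week-4 rates and correlations.

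Enrolment stays at 120. The cost is the loss of the claim that power was checked for the longitudinal model, and a real change to the wording of the primary test. Because the Trial status section reports recruitment complete with follow-up continuing, that change should be dated and made before allocation is revealed to the analysts.

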#### Statistical analysis

Data entry will be performed using Excel 2007 software (Microsoft, Redmond, WA, USA). IBM SPSS Statistics for Windows version 21.0 software (Armonk, NY, USA) will be used to analyze the collected data. All statistical analysis will be conducted by an independent statistician, with blinding of assessors maintained. A *p*-value <0.05 is considered statistically significant.

Descriptive statistics will be used to analyze baseline characteristics. To compare baseline demographic data between the treatment groups, independent *t*-tests (or the Mann–Whitney *U* test) will be used to analyze continuous data, and χ^2^ or Fisher’s exact tests will be used for categorical data.

In the main analysis, we will compare all subjects who are randomized in this study on an intention-to-treat basis, irrespective of whether they completed the allocated treatments. Data will be analyzed by using a longitudinal method (repeated-measures design). No missing data imputation will be implemented (e.g., mean imputation, last observation carried forward, multiple imputation). Instead, a linear mixed model (LMM) and a generalized linear mixed model (GLMM) that do not require formal imputation methods will be used [40]. Continuous dependent variables will be analyzed with LMM, fitted with restricted maximum likelihood estimation [41]. The multilevel approach (LMM and GLMM) will be used, as it accounts for the non-independence among observations in repeated-measures data and controls for the effect of individuals by including extra parameters to include any random effects [42]. Furthermore, a different covariance matrix can be specified, providing enhanced flexibility for longitudinal data analysis, as opposed to the traditional repeated-measures analysis of variance (ANOVA), which assumes compound symmetry (i.e., equal variances and covariances over time) [43]. Compound symmetry means that the pattern of covariances or correlations is constant across trials, which can be an unrealistic assumption. Mauchly’s test of sphericity in repeated-measures ANOVA is used to test whether sphericity (a less stringent form of compound symmetry) is met. Repeated-measures ANOVA must meet various assumptions, including compound symmetry, balanced data and complete dataset to ensure robust use.

The main outcome measure (responder analysis of ICIQ-UI-SF, dichotomous variable) and other dichotomous variables will be analyzed using GLMM (binomial logistic regression). We will estimate the marginal means of proportions, odds ratios comparing treatments and the corresponding 95 % confidence intervals. The fixed effects include time, code and interactions between code and time. Code comprises two binary coded variables, with the sham group set as the reference group. We are primarily interested in the code and time interaction, which represents the difference in outcome variables between groups.

For responder analysis of outcome measures, subjects who withdraw after randomization (missing data) will be considered as treatment failures and will be included in the denominator. The responder analysis between treatment groups will be compared using GLMM (binary logistic regression).

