### Study population

#### Inclusion criteria

To be eligible for participation, subjects are required to fulfill the following conditions: (1) female aged 21 years and older, (2) demonstration of urine leak on coughing at a bladder volume of approximately 200 to 250 ml, (3) International Consultation on Incontinence Questionnaire for Urinary Incontinence Short Form (ICIQ-UI-SF) score of at least 6 points (range: 0–21), (4) must be able and agree to carry out 1-hour pad test and (5) voluntary participation and signing of the informed consent form. Urodynamic testing will not be performed as an eligibility criterion [21].

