### Study outcomes

#### Primary outcome

The primary outcome measure is the improvement in the severity of involuntary urine loss. This is measured by the self-administered ICIQ-UI-SF, which measures frequency, volume and impact on daily life of involuntary urine loss. The ICIQ-UI-SF has undergone extensive psychometric testing and is graded A (highly recommended by the International Consultation of Incontinence) as an outcome measure in research trials [24]. The primary criterion for response is defined as having a 5-point or greater reduction in the ICIQ-UI-SF score (score range: 0–21) from baseline to 8 weeks [25–27]. The responder criterion of at least a 5-point decrease will allow detection of clinically significant improvement in SUI symptoms.

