Various measures will be taken to control for sources of bias. For selection bias, differences between the baseline characteristics of the two treatment groups will be compared to ensure that randomization is accomplished successfully. The appointed study nurse will sequentially open the envelopes, which will be counterchecked by another study nurse to ensure correct implementation of treatment assignments. To avoid performance and detection bias, the investigators are not allowed to be present in the treatment room. The appointed nurses who administer treatment will not be involved in enrolling the patients or in any outcome measure assessments. To evaluate the effectiveness of blinding of study participants, each subject will be asked to answer the following question at the end of the 16 treatment sessions: Which treatment do you think you received? The subject will have three possible answers: “active treatment”, “don’t know” or “sham treatment”. Patients’ ability to correctly identify treatment assignment at the end of the 8-week treatment will be analyzed and compared between the two treatment groups. Finally, to control for attrition bias, differences between the number of withdrawals from the study, including the reasons for withdrawal, will be analyzed and compared between the two treatment groups.

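### The stated primary responder model leaves out baseline ICIQ-UI-SF, giving up some power and leaving chance imbalance in severity uncorrected

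*Protocol article*

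**What the plan says.** Under Primary outcome the Protocol article states: "The primary criterion for response is defined as having a 5-point or greater reduction in the ICIQ-UI-SF score", from baseline to 8 weeks on a 0 to 21 scale. Inclusion criteria set the entry score at 6 or more.

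Under Statistical analysis, the responder outcome goes into a binomial logistic GLMM. Of its terms the section says: "The fixed effects include time, code and interactions between code and time". Code is the treatment arm, with sham as reference. Neither baseline ICIQ-UI-SF nor any other prognostic covariate is named there or elsewhere in the article.

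The Randomization section describes permuted blocks of four, six and eight, with no stratification by severity. Under Blinding and unblinding and control for bias, "differences between the baseline characteristics of the two treatment groups will be compared to ensure that randomization is accomplished successfully". Statistical analysis gives the tests for that comparison. No adjustment follows from it.

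Under Sample size calculation, "it is anticipated that MS will improve symptoms in 60 % (p1 = 0.6) of subjects with SUI" and "sham MS will improve symptoms in 30 % (p2 = 0.3) of subjects with SUI". This gives 44 per arm for 80% power, raised to 120 in total for 25% dropout.

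**The concern.** The outcome is a cut-off on change from baseline, so baseline enters its definition. A woman entering at 6 must reach 0 or 1 to respond; one entering at 16 needs only to reach 11. If the chance of response varies with entry score, a model without that score has two costs. It tests the treatment effect less efficiently than it could. It also leaves in the estimate any difference in severity that arises by chance between arms of 44 to 60 women.

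A comparison of baseline characteristics removes neither cost. If adjustment were added only after an imbalance had been seen, it would be post hoc.

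**Working it through.** **1. The plan's own figure.** Inputs: p1 = 0.60, p2 = 0.30, alpha 0.05 (taken as two-sided), power 80%.
- Pooled-variance formula: n = [1.96·√(2·0.45·0.55) + 0.842·√(0.24 + 0.21)]² / 0.30² = (1.379 + 0.565)² / 0.09 ≈ 42 per arm.
- Maximum-variance formula (p = 0.5): n = 2·0.25·(1.96 + 0.842)² / 0.09 = 43.6, so 44 per arm, which matches the protocol.
- Normal-approximation power is 81.9% at 44 per arm and 92.1% at 60 per arm.
- Dropout: 88 / 0.75 = 117.3, or 118 in even numbers; the protocol's goal is 120.

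The trial was therefore sized on an unadjusted comparison, and the unadjusted comparison delivers the planned power on those inputs.

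**2. Why baseline should be prognostic.** Write B for baseline, F for the week-8 score and rho for their correlation. Then Cov(B, B − F) = s_B² − rho·s_B·s_F. With equal SDs, the correlation of baseline with the size of the fall is √((1 − rho)/2): 0.63, 0.50 and 0.32 at rho = 0.2, 0.5 and 0.8. It vanishes only when rho = s_B/s_F. The article gives none of these quantities, so they are assumptions below.

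**3. Power with and without baseline.** Logistic regression of week-8 response on arm, then on arm plus baseline. This simplifies the GLMM to one time point. Assumptions: baseline normal, rounded and truncated to 6–21; equal SDs before and after; response calibrated to 60% versus 30%; 3,000 trials per row.

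| Baseline mean/SD before truncation | rho | 44 per arm | 60 per arm |
|---|---|---|---|
| 10/3 | 0.2 | 80.0% → 90.5% | 92.4% → 97.2% |
| 10/3 | 0.5 | 81.6% → 88.2% | 92.3% → 95.5% |
| 10/3 | 0.8 | 80.5% → 84.2% | 92.7% → 93.8% |
| 12/4 | 0.2 | 81.4% → 92.4% | 92.1% → 97.5% |
| 12/4 | 0.5 | 81.3% → 87.9% | 92.8% → 96.0% |
| 12/4 | 0.8 | 80.3% → 84.3% | 92.2% → 93.1% |

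The gains are 3.7 to 11.0 points at 44 per arm and 0.9 to 5.4 at 60. A direct logistic simulation with an odds ratio of 1.65 per baseline SD gives 80.9% → 84.0% at 44 per arm, so the range is about 3 to 11. Fixing the follow-up SD at 4 instead gives about 1 to 9 and 0 to 4. With a baseline odds ratio of 1 there is no gain. In the tabulated scenarios, sham response is 2–15% at baseline 7 or below and 40–68% at 13 or above.

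**4. Chance imbalance.** The standard error of the difference in mean baseline at 60 per arm is √(2/60) = 0.183 SD. An imbalance of that size shifts the 30-point difference by 1.9, 2.9, 3.4 and 4.4 points for baseline odds ratios per SD of 1.65, 2.23, 2.72 and 4.48. It can go in either direction.

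**5. Dropouts counted as failures.** The protocol counts withdrawals as treatment failures. With 25% in each arm, 0.75·0.60 = 0.45 and 0.75·0.30 = 0.225. At 60 per arm, unadjusted power is 74.7%. Adjusted power is 75.3% at an odds ratio of 1.35 per SD (unadjusted 74.2% in those runs) and 86.6% at 4.48 (unadjusted 74.7%), a gain of about 1 to 12 points. The upper end assumes that baseline predicts the composite of dropout and non-response that strongly. If dropout is unrelated to baseline the link is diluted, and the gain is roughly 1 to 7.

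**6. Type I error.** At 30% in both arms the rejection rate was 3.9% to 5.5%, with and without baseline.

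**The case against.** The strongest defence is that nothing here is wrong. Randomisation makes the unadjusted comparison valid, its type I error is near 5%, and the sample size was set for it. All of that stands. A reader might infer that the omission biases the trial or leaves it below its planned power; step 1 and step 6 do not support that. The power of about 75% in step 5 comes from counting dropouts as failures, not from leaving out baseline.

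A reader might also infer that baseline decides who is able to respond. It does not: with entry at 6 or more, every eligible woman can fall by 5 points. Baseline changes how far down the scale she must go, and the documents do not say how strongly that affects response.

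The article introduces the terms with the word include, and a fuller analysis plan may exist. That lowers certainty but does not supply the term: the article lists the model's fixed effects, and baseline is not among them. The subject-level random effects mentioned in the same section handle within-woman correlation and do not adjust the arm contrast for baseline. Nor does the time factor, because a responder outcome defined by change has no baseline value.

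One objection limits the remedy. The sample size section refers to six repeated measurements, and Table 1 shows six ICIQ-UI-SF assessments only if baseline is counted. In the linear mixed models baseline may therefore already be a time level of the response. Adding it as a covariate there would put it on both sides.

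**Conclusion.** The point holds as an inexpensive improvement, not as an error in the plan. The stated primary responder model omits a covariate that is linked to the endpoint by its definition and is collected on every woman, and no other planned step corrects a chance imbalance in it.

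The direction is well founded; the size is not known. The ranges in the working rest on assumed baseline distributions, SDs and correlations, on a single-time-point version of the model and, for the dropout case, on equal dropout in both arms. They shrink to nothing if baseline is not prognostic. How baseline characteristics are tabulated or tested, and whether the continuous score should also be analysed, are separate matters that this point does not settle.

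**What to change.** Before unblinding:
- Add baseline ICIQ-UI-SF total score as a continuous fixed covariate in the primary responder GLMM.
- Do the same in the other responder models, using the matching baseline value where one exists. Table 1 shows none for PGI-I.
- Report the week-8 effect as a standardised difference in proportions with a 95% confidence interval: average each woman's predicted probability under active and under sham over all randomised women, then subtract. The adjusted odds ratio is conditional on baseline and is not directly comparable with the unadjusted one, so it should not be the only summary.
- For the continuous outcomes, state whether baseline is a time level of the response. Add a baseline covariate only if it is not.

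The cost is a few lines of analysis wording. Baseline ICIQ-UI-SF is an eligibility item recorded at visit 0, so it should be known for every randomised woman. The Trial status section reports recruitment complete with follow-up continuing, so no visit, measurement or sample size needs to change.
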